### Study design

To meet our specific objectives, we will conduct a parallel-group interrupted time series RCT with 32 U.S. SSPs randomized to receive SAIA-SSP-HIV or IAU for 12 months (n = 16 organizations per arm; Fig 1). SSPs randomized to the IAU arm will not receive the active SAIA strategy or any support from SAIA specialists (i.e., IAU is characterized by the absence of SAIA-SSP-HIV).

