### Recruitment and pre-randomization procedures

We will recruit SSPs from 01/12/2023 to 01/07/2025. Organizations will be considered eligible for the trial if they meet the following inclusion criteria: (1) located in a U.S. state, territory, or tribal nation, (2) operate a dedicated SSP that provides access to sterile syringes and injection equipment, and (3) have directly provided their own (i.e., not through referrals to external organizations) HIV testing services to participants within the past 30 days. SSPs will be excluded if they (1) are participating or have participated in other studies involving SAIA or its key components, or (2) intend to stop providing HIV testing services to participants within the next 21 months.

Initial recruitment efforts will be targeted towards SSPs known to our national investigator team through previous research. From there, we will leverage publicly available SSP organizational directories (e.g., the North American Syringe Exchange Network [NASEN]). Study coordinators will first email identified SSPs’ directors (e.g., executive director, chief executive officer) to briefly describe the study and request an introductory call to provide greater detail on study procedures. For SSPs expressing interest in enrolling in the study, the coordinator will set up an enrollment appointment using Zoom’s web-enabled audio and screen-sharing technology and assign a unique identification code. Recruitment will occur over 15 months, targeting two to three enrollments per month. If an SSP declines or fails to respond after three contact attempts, we will replace the organization with another potentially eligible SSP.

Following enrollment, SSPs will enter a three-month lead-in period beginning on the first day of the month they are enrolled in. During lead-in, SSPs will be asked to submit data on outcomes (HIV testing and referrals) for the month prior, disaggregated by week. Outcome data, described in greater detail below*,* will include total numbers of SSP participant encounters, HIV tests conducted, and referrals to appropriate clinical services. Outcome data will be collected using an online survey distributed automatically through REDCap, a secure online platform for managing research project surveys. Study coordinators will provide technical support to SSPs as needed to ensure timely and complete outcome data submissions.

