### Analyses and power calculations

Statistical analyses will be conducted in Stata (College Station, TX) using a single-blinded approach. Before model fitting under Objectives 1 and 2, we will assess whether there is significant variation across the three (potential) levels of aggregation for each set of key outcomes and implementation measures: (1) within-SSP level (repeated measures over time), (2) between-SSP level, and (3) SSP type (local health jurisdiction/clinic or community-based organization). We will also assess changes in outcomes over time by examining functional form. We assume that there will be piecewise linear change during the three-month lead-in period, post-implementation from baseline through 18 months, and treatment effect “deterioration” between 12 and 18 months, though non-linear functional forms may be necessary given the large number of assessments. We will also account for the total number of participant encounters for the number of HIV tests conducted outcome, and the number of HIV tests conducted for the number of referrals outcome.

For Level 1 (within-SSP), we will estimate three random effects as growth over time. On the basis of the structure of the time steps with *α*_pis_, we will estimate a random intercept (*π*_*0is*_), which is the estimated (conditional) mean value of the outcome at time =  0 (e.g., run-in baseline) and two random slopes (*π*_*1is*_*, π*_*2is*_): (1) the estimate per-year change in Y from the run-in phase through 18 months and (2) the “deterioration” phase, capturing how much reduction there is in change over the last year, if any, for the SAIA arm. These values will vary across SSP *i* within county *s*. In Level 2 (between-SSP), the Level-1 intercept and slopes will be the outcomes at Level 2.

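### The growth model has no calendar-time term although SSPs enter over 15 to 19 months, so any residual seasonal cycle in testing becomes noise in the 6-month sustainment contrast; two calendar terms would remove most of it

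*Protocol article*

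**What the plan says.** All references are to the protocol article.

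**Time structure (Analyses and power calculations).** The section states: "For Level 1 (within-SSP), we will estimate three random effects as growth over time". The intercept is described as a quantity "which is the estimated (conditional) mean value of the outcome at time" zero, with the run-in baseline given as the example. The first slope is "the estimate per-year change in Y from the run-in phase through 18 months", and the second captures deterioration in the last phase. Arm enters at Level 2 and SSP type at Level 3. Non-linear shapes are left open ("though non-linear functional forms may be necessary given the large number of assessments"), but as shapes of change over study time. No calendar or seasonal term is named, either here or in the description of the power simulation.

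**Adjustment for volume (same section).** "We will also account for the total number of participant encounters for the number of HIV tests conducted outcome"; referrals are adjusted for the number of tests in the same way.

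**Reading of Objective 2 (same section).** If the sustainment-phase term does not differ significantly by arm, the plan takes first-year gains to have been maintained.

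**Entry (Recruitment and pre-randomization procedures).** "Recruitment will occur over 15 months, targeting two to three enrollments per month". The recruitment dates in the same section span 19 months when read as day/month. Each SSP's lead-in starts in its enrollment month, and randomization follows at the end of the lead-in, stratified by organization type only.

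**Design (Study design).** A "parallel-group interrupted time series RCT with 32 U.S. SSPs", 16 per arm.

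**The concern.** Each SSP's sustainment phase covers one half-year, and its entry month decides which half. Half of an annual cycle looks much like a straight rise or fall. An SSP whose sustainment runs from a seasonal peak to a trough appears to deteriorate, and one that runs the other way appears to improve. With time measured only from run-in, the model has nothing to attribute this to except SSP-specific slope variation.

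Randomization makes entry month independent of arm, so the arm contrast is right on average. What is lost is precision, with only 16 SSPs per arm to average it out.

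The loss matters more than usual here because of how Objective 2 is read. When a non-significant deterioration term is taken as success, extra variance makes the favorable reading easier to reach: real deterioration is more easily missed and reported as a sustained effect. A correct type I error rate gives no protection against that.

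**Working it through.** **Inputs from the protocol article.** 3 + 12 + 6 months of weekly data (13 + 52 + 26 = 91 weeks); 16 SSPs per arm; weekly mean 7.32, SD 2.94; d = 0.8 for the main effects; d = 0.48 for detectable deterioration at power 0.80.

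**Assumptions, not in the documents.** An annual cycle common to all SSPs with amplitude a, as a share of 7.32; calendar phase spread evenly over SSPs; within-SSP residual SD 2.0; two-sided alpha 0.05.

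**1. The plan's own figures.** 0.8 × 2.94 = 2.352 (stated 2.35). 2.352 / 11 = 0.214 per week (stated .21). Both reproduce. The power claims cannot be reproduced exactly because the pilot random effects are not given.

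**2. Variance of the deterioration contrast.** The deterioration coefficient for one SSP is a weighted sum of its weekly values with least-squares weights c(t). Its variance has two parts:
- noise: SD = 2.0 × √Σc²
- season: SD = a × 7.32 × |Σ c(t)·exp(iωt)| / √2, with ω = 2π/52.18 per week

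The SE of the arm contrast is √(2/16) × √(noise² + season²), so the inflation factor is √(1 + (season/noise)²). It was computed for two readings of the model.

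| Reading | Noise SD per SSP (per week) | Season SD at 10% / 20% | SE inflation at 10% / 20% |
|---|---|---|---|
| Slope from run-in, change at month 12 after randomization (91 weeks) | 0.0441 | 0.0311 / 0.0622 | 1.22 / 1.73 |
| Post-randomization weeks only, change at month 12 (78 weeks) | 0.0487 | 0.0533 / 0.1065 | 1.48 / 2.40 |

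For example, √(1 + (0.0311/0.0441)²) = 1.22. At 0% the factor is 1 by construction.

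Simulation with entry spread over 15 or 19 months agrees. With the slope starting at randomization, the SD of the arm contrast is 0.016 per week with no season, 0.021 at 10% and 0.028 to 0.030 at 20%. A separate simulation gave 0.017, 0.025 and 0.041, ratios of 0.025/0.017 = 1.47 and 0.041/0.017 = 2.41. Mean differences stayed near 0, and type I error was 0.04 to 0.06.

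**3. Sensitivity to residual SD.** If the whole stated SD of 2.94 were residual, the first-row noise becomes 0.0441 × 2.94/2.0 = 0.0648. The factors fall to √(1 + (0.0311/0.0648)²) = 1.11 and √(1 + (0.0622/0.0648)²) = 1.39.

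**4. The other terms.** The run-in-to-18-month slope is inflated by 1.00, 1.01 and 1.03 at 10%, 20% and 30%. Power for the d = 0.8 mean shift stays at or above 0.98 throughout.

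**5. Anchored to the plan's deterioration power.** Read d = 0.48 as 0.48 × 2.94 = 1.41 tests over 26 weeks, or 0.0543 per week, and suppose the plan's simulation contained no season. Power 0.80 then implies SE = 0.0543 / (1.960 + 0.842) = 0.0194, a per-SSP SD of 0.0194 × √8 = 0.0548. Adding the first-row season:
- 10%: √(0.0548² + 0.0311²) = 0.0630, SE 0.0223, power 0.68
- 20%: √(0.0548² + 0.0622²) = 0.0829, SE 0.0293, power 0.46

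On this anchor the SE inflation is 0.0630/0.0548 = 1.15 and 0.0829/0.0548 = 1.51. If the encounter adjustment removes half of the swing, power is 0.77 and 0.68. Under the plan's reading, the chance of calling such deterioration maintained is 1 minus power: 20% with no season, 32% and 54% unadjusted, 23% and 32% with half the swing removed.

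**6. With the calendar terms.** A common sine and cosine pair returns the SD of the contrast to about 0.016 to 0.017 at every amplitude, and costs essentially nothing when there is no season. If seasonal phase differs between SSPs, recovery is partial: about 0.022 at 10% and 0.031 at 20%, against 0.025 and 0.041 without the terms.

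**The case against.** The strongest reply is that nothing in the article is wrong. Seasonal covariates are often left to a statistical analysis plan, which is not shown; functional form is to be examined before fitting; and no document reports any seasonality in testing. Part of this stands: the size is conditional throughout, and the point cannot be called an error. But the article itself fixes the time origin, the slopes and the reading of the sustainment term, and the comment is on that stated structure. A curve in study time does not cure it, because with staggered entry a common calendar cycle falls at different study times in different SSPs.

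The second reply is the planned volume adjustment. It stands in large part. Seasonality that acts through footfall is removed from tests by adjusting for encounters, and swings in testing volume are removed from referrals by adjusting for tests. Only a cycle in the share tested or referred remains, so the unadjusted figures are upper readings for a given amplitude.

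The third is that SSPs across U.S. states, territories and tribal nations may not share one season. That stands too, and limits the gain to a partial one.

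A reader might go further and infer that the lead-in slope is distorted. The Level-1 model as written has no separate random lead-in slope: the first slope runs from run-in through 18 months and averages over more than a full year. The phrase "We assume that there will be piecewise linear change during the three-month lead-in period" hints at a lead-in segment, but the listed random effects do not include one.

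**Conclusion.** The point holds as a precision issue for Objective 2. The model as described uses study time only while entry is staggered, and any calendar cycle left after volume adjustment inflates the variance of the deterioration contrast. With residual SD 2.0 and before encounter adjustment, the SE rises about 1.2 to 1.5 fold at 10% amplitude and 1.7 to 2.4 fold at 20%. It rises less if residual variation is larger or the contrast is anchored to the plan's stated power, and not at all without seasonality. Amplitude, residual SD and a shared phase are all assumptions.

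A reader might infer bias, or a threat to the 12-month comparison. Neither follows: entry month is independent of arm by randomization, simulated type I error stays near 5%, the run-in-to-18-month slope is inflated by at most 1.03, and power for the mean shift remains at least 0.98. What makes the point worth acting on is the combination of a short window, few clusters and a rule that treats non-significance as maintained gains.

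**What to change.** In the models for both outcomes, add one annual sine and cosine pair as fixed effects common to all SSPs, derived from the calendar date of each reported week. Keep the study-time terms, the volume adjustment and SSP type as planned. Prespecify the pair rather than adding it after a look at the data.

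**Cost.** One line in the analysis plan and 2 degrees of freedom out of at most 32 × 91 = 2,912 SSP-weeks. No new data are needed, because outcomes are already submitted by week.

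**Downside.** No gain if there is no seasonality, and only part of the gain if seasonal phase differs between SSPs.

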*Β*_*pqs*_ is a matrix of coefficients corresponding to the effect of between-individual predictor *q* on Level-1 outcome *p* (intercept, slope) within SSP *s*. The key predictor included in *χ*_*qis*_ is a 0/1 dummy indicator indicating whether SSP *i* was in the SAIA condition or IAU. *Β*_*1s*_ will capture the average change over time in HIV testing and referrals to appropriate clinical services for HIV prevention and treatment, which (1) should not be significantly different from zero during the lead-in period, and (2) will vary by SAIA and IAU after implementation (by virtue of the SAIA x time period 1 interaction). *Β*_*0s*_ will capture the conditional mean level of study outcomes, which, if it varies by treatment condition, would capture a mean shift in our study outcomes. *Β*_*2s*_ will capture the change over time in study outcomes during the sustainment period; if it interacts with the SAIA indicator, it will capture slope differences over time beyond 1 year between SAIA and the IAU condition, with Year 1 gains maintained if this parameter estimate is not significant. Level 3 will capture SSP type-level variability in intercepts and, if necessary, slopes over time.

The main analyses will be modeled under full information maximum likelihood and supplemented by multiple imputation for missing data on key predictors for models under Objectives 1 and 2. Both produce accurate estimates and standard errors under the assumption that missingness is predictable by variables that are observed but unrelated to the values that are missing themselves (i.e., missing-at-random). Results from outcomes analyses across 20 multiply-imputed datasets are then combined, accounting for both between-imputation and within-imputation variation. In assessing sensitivity to the missing-at-random assumption, we may explore latent pattern mixture models for non-ignorable missingness. These methods have been utilized in other studies conducted by members of the research team.

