We structured a Monte Carlo power analysis for Objectives 1 and 2 by structuring a population model reflecting weekly assessments for a 3-month lead-in period, a 12-month active intervention phase, and a 6-month sustainment period. The mean and standard deviation of the number of people who test for HIV in the target SSPs was 7.32 (2.94); these values were used as the run-in period mean and SD in the simulation. Effect sizes from a pilot study that used a similar SAIA platform ranged from.48 to 1.50; thus, we power the current study in anticipation of large effect sizes (d = .8). The mean shift in post-implementation outcomes favoring SAIA that corresponds to an effect size of.8 would be an additional 2.35 people tested under SAIA. The per-week increase in number tested under SAIA to reach a longitudinal Cohen’s d effect size of.8 by 11 weeks would be an increase of.21 persons per week. We generated 250 synthetic samples of n = 32 and analyzed the samples in Mplus while imposing (a) the random effect structure from pilot estimates and (b) a state-level ICC of.05. Power to detect a post-implementation mean shift and differences in slopes over time were greater than 80%. Detecting treatment effect deterioration from months 1–12 to month 13–18 for power of.80 requires deterioration equivalent to a Cohen’s d of.48; despite a sample size of 32, the extremely large number of repeated measures offsets the sample size with regard to statistical power to detect slope differences.

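### The trial is powered for a post-implementation mean shift, but none of the three stated SSP random effects covers such a step, so its standard error may be too small

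*Protocol article*

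**What the plan says.** All of the relevant text is in the protocol article, mostly under Analyses and power calculations.

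- **Random effects.** At the within-SSP level, "we will estimate three random effects as growth over time". They are an intercept, "which is the estimated (conditional) mean value of the outcome at time" zero (the example given is the run-in baseline), a slope from run-in through 18 months, and a slope for the deterioration phase. A further level captures variability by SSP type.
- **The shift.** The coefficient B0 belongs to that intercept, "which, if it varies by treatment condition, would capture a mean shift in our study outcomes".
- **Power.** The simulation used "weekly assessments for a 3-month lead-in period, a 12-month active intervention phase, and a 6-month sustainment period", and the result reads "Power to detect a post-implementation mean shift and differences in slopes over time were greater than 80" percent. The shift at d = 0.8 is 2.35 people tested.
- **Clusters.** Study design gives "32 U.S. SSPs randomized to receive SAIA-SSP-HIV or IAU for 12 months", 16 per arm.
- **Timing.** Recruitment and pre-randomization procedures places randomization at the end of the three-month lead-in.
- **Estimation.** Full information maximum likelihood. The article gives no residual correlation structure and no robust standard error, and it does not state independence either.

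**The concern.** Time zero in this model is the run-in baseline, and SSPs are randomized three months later. An arm difference in the intercept is therefore a difference that existed before allocation and cannot be the effect of SAIA. The effect in the power statement needs a separate arm-by-post-implementation step.

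Once that step is added, no SSP-level variance component supports it. If weekly residuals are treated as independent, the model counts 91 weeks per programme as nearly separate information about the step. Weekly testing counts at one programme plausibly carry over through staffing, funding and quality-improvement solutions that run for at least four weeks. Programmes may also change level by different amounts for local reasons. Either makes the stated standard error too small and the p-value too optimistic, for one of the two effects on which the trial is powered.

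**Working it through.** **Reproducing the plan's figures.** 0.8 × 2.94 = 2.352, matching 2.35; 2.35 / 11 = 0.214, matching .21. With one measurement per SSP, SE = 2.94 × √(2/16) = 1.04 and power is 62%. With weekly data and independent residuals, power for the step is well above 80% (rows for ρ = 0 below), so the power claim is consistent on that basis. The article gives no exact power figure and no variance split to match.

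**Inputs from the article.** 32 SSPs, 16 per arm; mean 7.32, SD 2.94; shift 2.35; weekly data, taken as 13 + 52 + 26 = 91 weeks.

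**Assumptions.** Lag-1 correlation ρ; weekly error variance 7.32; random-intercept variance 2.94² − 7.32 = 8.64 − 7.32 = 1.32; variance 1 per year² for each slope.

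**Method.** Let Z hold the intercept, time and deterioration terms, and X hold Z plus a step at week 13. The fitted covariance is V_m = Z D Z′ + σ²I, at the values that maximum likelihood approaches in large samples. The true covariance V replaces the independent errors by autocorrelated ones. With B = (X′V_m⁻¹X)⁻¹, for the step coefficient:

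- model variance = (2/16) × B
- true variance = (2/16) × B X′V_m⁻¹ V V_m⁻¹X B
- type I error = 2[1 − Φ(1.96 × SE_model / SE_true)]
- power with a correct critical value ≈ Φ(2.35 / SE_true − 1.96)

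| Time terms | ρ | SE model | SE true | Type I error | Power |
|---|---|---|---|---|---|
| No separate lead-in slope | 0 | 0.397 | 0.397 | 5% | >99% |
| | 0.1 | 0.396 | 0.435 | 7% | >99% |
| | 0.3 | 0.392 | 0.524 | 14% | 99% |
| | 0.5 | 0.385 | 0.642 | 24% | 95% |
| Separate lead-in slope | 0 | 0.616 | 0.616 | 5% | 97% |
| | 0.1 | 0.614 | 0.665 | 7% | 94% |
| | 0.3 | 0.608 | 0.777 | 12% | 86% |
| | 0.5 | 0.597 | 0.908 | 20% | 74% |

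Example: at ρ = 0.3 without a lead-in slope, 1.96 × 0.392 / 0.524 = 1.47, and 2[1 − Φ(1.47)] = 14%.

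**Simulation.** Fitting the stated random effects to simulated data gave 5.8%, 12% and 20% at ρ = 0, 0.3 and 0.5. A second set under other variance assumptions gave 5%, 13–15% and 19–24%. In the first set the true SE was 0.75, 0.87 and 1.01 at ρ = 0.3, 0.5 and 0.7, so power is Φ(2.35/0.75 − 1.96) = 88%, then 77% and 64%.

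**Only the variance beyond Poisson noise autocorrelated.** If 2.94 is the total weekly SD and counts carry Poisson variance 7.32, only 1.32 / 8.64 = 15% of the variance can be autocorrelated. Type I error is then 7–8% for short memory (lag-1 correlation 0.5 in that part) and about 8–16% at 0.8 to 0.95.

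**No autocorrelation, programme-specific shifts.** With shift SDs of 0.5, 0.75 and 1.0 tests per week, type I error is 7%, 10% and 14% without a separate lead-in slope, and 6%, 7% and 9% with one.

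**Remedies checked.** Adding a first-order autoregressive residual to the three random effects gave 4.8% (ρ = 0.3) and 5.6% (ρ = 0.6). Comparing SSP-level step estimates by a t-test on 30 df gave 4.3–5.8%. Analysis of covariance of the 12-month mean on the lead-in mean gave 3–4%.

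**The case against.** The strongest reply is that the article does place the shift on a term with a random effect: B0 belongs to the random intercept. On that literal reading the arm test rejects at 4.5–8.8% with an unstructured random-effects covariance and 6–11% with a diagonal one, and the unstructured results show no trend with ρ. This stands as arithmetic, but it does not rescue the plan. An intercept at run-in baseline cannot measure a post-implementation change. Run-in is given only as an example of time zero, but moving the origin would not help: without a step, an arm difference in the intercept still mixes pre-existing with new differences.

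Second, independent residuals are not stated, and a condensed article may leave the residual covariance to the full plan. This also stands, so the inflation is conditional. What the article does fix is the list of random effects and a powered effect that the list does not cover.

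Third, ρ is assumed. This stands too. At 0.1, or with short-memory correlation beyond Poisson noise, the error is only about 7–8%.

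A reader might also infer that a planned comparison of lead-in trends between arms would raise false alarms, because a coefficient "should not be significantly different from zero during the lead-in period". That sentence concerns the average change over time; the arm contrast is placed after implementation, so no such check is stated. Likewise, the remark that "the extremely large number of repeated measures offsets the sample size" is made about slope differences and is not evidence of how the shift was powered.

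**Conclusion.** The point holds in conditional form. The stated random effects do not cover the post-implementation shift, and the coefficient named for it is defined before randomization. If the shift is tested as a step under independent weekly residuals, nominal 5% becomes about 7% at ρ = 0.1, 12–15% at 0.3 and 19–24% at 0.5 when all residual variance is autocorrelated. It becomes about 7–15% (16% in one setting) when only variance beyond Poisson noise is, and 6–14% with no autocorrelation but programme-specific shifts of SD 0.5–1.0. These rest on assumed correlations and variances that the article does not give.

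It would go too far to say that the planned test rejects far more than 5% of the time, or that the power figure is wrong. The first needs the step reading with moderate or persistent correlation, or sizeable programme-specific shifts. On the second, model-based power stays above 80% at ρ = 0.3 (86–88% even with a separate lead-in slope). At 0.5 it is 74–77% with that slope and about 95% without it. A less efficient SSP-by-SSP test with its own lead-in slope gave 76% at 0.3, so the time terms matter. This should be corrected before analysis; it does not invalidate the design.

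**What to change.** 1. Define the mean shift as an arm-by-post-implementation term, separate from the run-in intercept.
2. Give that term an SSP random effect and use a first-order autoregressive weekly residual, or use cluster-robust standard errors with small-sample degrees of freedom. Alternatively, test each SSP's 12-month mean adjusted for its lead-in mean and SSP type, with t critical values. That alternative estimates the average difference over the year, not an immediate step, so the choice should be stated.
3. Re-run the Monte Carlo power under the chosen time terms and error structure, over a stated range of ρ, and restate the figure if it changes.

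The cost is a few lines of Stata code and one repeated simulation. Intervals will be somewhat wider and the stated power for the shift may be less favourable.

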## Materials and methods

### Aims, objectives, and hypotheses

The overall aim of this study is to assess the impact of SAIA-SSP-HIV on U.S. SSPs’ delivery of HIV testing and referrals to appropriate clinical services, as compared to an implementation-as-usual (IAU) condition. The specific objectives and related hypotheses of this organizational-level interrupted time series randomized controlled implementation trial include:

To test the effectiveness of SAIA-SSP-HIV on improving SSPs’ delivery of HIV testing and referrals to appropriate clinical services (i.e., for HIV prevention or treatment, depending on HIV testing results). We hypothesize that, compared to the IAU arm, SSPs randomized to the SAIA-SSP-HIV arm will demonstrate significantly higher proportions of participants receiving HIV testing and referrals over a 12-month implementation period.To test the sustained effectiveness of SAIA-SSP-HIV on improving SSPs’ delivery of HIV testing and referrals to appropriate clinical services. We hypothesize that, compared to IAU, SSPs randomized to SAIA-SSP-HIV will sustain higher proportions of participants receiving HIV testing and referrals during a 6-month sustainment period (i.e., 6 months after the active treatment phase).To estimate the costs and cost-effectiveness of SAIA-SSP-HIV on improving SSPs’ delivery of HIV testing and referrals to appropriate clinical services. We hypothesize that SAIA-SSP-HIV will be cost-effective at increasing the proportions of participants receiving HIV testing and referrals compared to SSPs randomized to IAU.

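### Sustainment is inferred from a non-significant slope term, so a real loss of a third to a half of the year-1 gain could often be reported as gains maintained

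*Protocol article*

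**What the plan says.** Three statements in the protocol article bear on this point.

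- **Hypothesis** (Aims, objectives, and hypotheses, second objective): "compared to IAU, SSPs randomized to SAIA-SSP-HIV will sustain higher proportions of participants receiving HIV testing and referrals during a 6-month sustainment period". This compares the level of the two arms during sustainment.
- **Decision rule** (Analyses and power calculations, paragraph on the coefficients): the sustainment-slope coefficient, when it interacts with the SAIA indicator, shows slope differences between arms after one year, "with Year 1 gains maintained if this parameter estimate is not significant". The article attaches no retention margin, confidence-interval criterion or named months 13–18 contrast to this rule.
- **Power** (same section): "Detecting treatment effect deterioration from months 1–12 to month 13–18 for power of.80 requires deterioration equivalent to a Cohen’s d of.48". The planned effect is d = 0.8, or 2.35 more people tested, on a run-in SD of 2.94.

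The second slope is also described twice in that section. In the Level 1 paragraph the first slope is "the estimate per-year change in Y from the run-in phase through 18 months" and the second is "capturing how much reduction there is in change over the last year, if any, for the SAIA arm", so the second is an increment on a slope that already covers the sustainment months. In the coefficients paragraph the corresponding term "will capture the change over time in study outcomes during the sustainment period", which is a slope in its own right.

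**The concern.** A non-significant interaction means that the data did not rule out zero deterioration. It does not mean that they ruled out a deterioration that matters. Under the stated rule, the less precise the estimate, the more likely the favourable conclusion: noisy reporting or loss of SSPs makes maintained easier to declare.

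The rule also answers a different question from Objective 2. If SAIA produced no gain in year 1 and the arms then ran in parallel, the interaction would be null and the rule would report that gains were maintained. Conversely, SAIA could remain clearly above IAU throughout months 13–18 and still show a significant negative slope. Sustained effectiveness is one of the trial's three objectives, so the wording of this inference matters.

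**Working it through.** **Inputs, all from Analyses and power calculations.** Run-in SD 2.94; planned effect d = 0.80; deterioration detectable with 80% power d = 0.48; pilot effects 0.48 to 1.50. The significance level is not stated; two-sided 5% is assumed, with one-sided 5% shown as the alternative.

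**1. The plan's own figures.** 0.80 × 2.94 = 2.352 (stated 2.35), and 2.352 / 11 = 0.214 per week (stated 0.21), so both reproduce. The d = 0.48 threshold cannot be reproduced because the random-effect structure taken from the pilot is not given. It is accepted as stated.

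**2. Detectable loss as a share of the gain.** 0.48 / 0.80 = 60%, or 0.48 × 2.94 = 1.41 of 2.35 people.

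**3. Implied standard error.** SE = 0.48 / (1.960 + 0.842) = 0.171 two-sided; 0.48 / (1.645 + 0.842) = 0.193 one-sided.

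**4. Chance of a maintained conclusion after a true loss L.** P = 1 − Φ(L/SE − z).

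| True loss of the 0.80 gain | L (d) | People | Two-sided | One-sided |
|---|---|---|---|---|
| One third | 0.267 | 0.78 | 66% | 60% |
| One half | 0.400 | 1.18 | 35% | 33% |
| 60% | 0.480 | 1.41 | 20% | 20% |

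The largest observed loss that stays non-significant is 1.960 × 0.171 = 0.336, or 42% of the gain.

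**5. Sensitivity to the size of the gain (two-sided).** At the pilot's lower value, 0.48, a loss of a third or a half is called maintained 85% or 71% of the time. At its upper value, 1.50, the figures are 17% and 1%.

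**6. The two slope definitions.** Suppose, as an illustration not taken from the protocol, that the gain climbs linearly to 2.352 at week 52 and is then held.

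- Incremental coding (Level 1 paragraph): slope 1 = 2.352 / 52 = 0.045 per week, so slope 2 = −0.045 per week. Over 26 weeks that is −1.18 people, or d = −0.40. At SE 0.171 it is flagged as deterioration about 65% of the time.
- Separate sustainment slope (coefficients paragraph): slope 2 = 0, so no deterioration is indicated.
- If the gain arrives as a step and is held, slope 2 = 0 under both codings.

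Under the incremental coding with the same ramp, a true loss of a third gives a contrast of 0.40 + 0.267 = 0.67, detected about 97% of the time. A loss of a half gives 0.40 + 0.40 = 0.80, detected about 99.7% of the time.

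**The case against.** The strongest reply has four parts.

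- **The percentages are conditional.** They need an assumed significance level, a true gain of 0.80, and d = 0.48 on the same scale as that gain. The power statement describes deterioration between two periods, which may not be the same quantity as a slope loss by month 18. This stands, and the figures are offered on those terms. The fault in the rule does not depend on them.
- **The model can already deliver the Objective 2 contrast.** It carries SAIA effects on the intercept and both slopes, so the months 13–18 difference can be derived, and a condensed article may leave the contrast to the analysis plan. That is fair as to what is omitted. But the article does not stay silent: it states a decision rule, and that rule is neither the hypothesis nor a valid test of maintenance.
- **A reader might infer that the rule errs in both directions**, missing real losses and also calling a held plateau a loss. The documents do not support this as one claim. The missed losses in step 4 arise where the tested term equals the loss, as with a separate sustainment slope or a step gain. The false loss arises only with the incremental coding and a ramped gain, and there losses of a third to a half are nearly always detected. The article also says that functional form will be examined and that non-linear forms may be needed, which could deal with a visible plateau.
- **A reader might also infer that an observed loss of half would pass as maintained.** It would not: at the implied SE, an observed loss above 42% of the gain is significant. The 35% refers to a true loss of half.

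**Conclusion.** The non-significance rule is wrong as written, under either definition of the second slope. If the year-1 gain is 0.80, testing is two-sided at 5%, and 0.48 and 0.80 share a scale, a true loss of one third or one half would be reported as maintained about 66% or 35% of the time. The risk is larger if the gain is nearer the pilot's lower value and small if it is nearer the upper. The rule also does not test the between-arm level difference that Objective 2 states.

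The two descriptions of the second slope are a separate inconsistency. They must be reconciled because, with a ramped gain, the same held result can be read as kept or lost depending on which description is followed. That is as far as the plateau point goes. Objective 1 is not affected.

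**What to change.** 1. Delete the sentence that infers maintenance from a non-significant term.
2. Define the second slope once, either as a change from slope 1 or as the slope within the sustainment period, and use that definition in both the Level 1 and the coefficients paragraphs.
3. Test Objective 2 as the SAIA–IAU difference over months 13–18, adjusted for the lead-in, with a 95% CI.
4. Report the change in the SAIA–IAU difference from month 12 to month 18 with its CI. Use the word maintained only if that CI excludes a loss fixed before analysis.

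Do not use the ratio of the months 13–18 effect to the months 1–12 effect as a retained share. If the gain ramps linearly from 0 to g over year 1, its year-1 mean is g/2. If it then falls linearly to zero by month 18, its sustainment mean is also g/2, so the ratio shows 100% retention after complete loss.

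**Cost.** Items 1 to 3 change wording and specification and need no new data. Item 4 makes the claim harder to earn. At SE 0.171 with no true loss, the power to exclude loss of half the gain (margin 0.40) is Φ(0.40/0.171 − 1.96), about 65%. For a quarter of the gain (margin 0.20) it is about 21%. Reaching 80% would need an SE of 0.143 or 0.071. Both margins are illustrative; the choice belongs to the investigators.
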